### **Safety analysis**

At each follow-up visit, the following parameters will be computed:

- ◆ Percentage and number of subjects experiencing immediate reactions within 30 minutes of vaccinations.
- ◆ Number and percentage of subjects with at least one local reaction (within 72 hours after each injection), with the frequencies of each type of local reactions (global and broken down according to the size of the reaction when appropriate)
- ◆ Number and percentage of subjects with at least one systemic event (within 72 hours after each injection either related or non related to the vaccine), with the frequencies of each type of event (global and broken down according to the relationship and the severity)
- ◆ Number and percentage of subjects with at least one local reaction (within 72 hours to one month after each injection), with the frequencies of each type of local reactions (global and broken down according to the size of the reaction when appropriate)
- ◆ Number and percentage of subjects with at least one systemic event (within 72 hours to 1 month after each injection either related or non related to the vaccine), with the frequencies of each type of event (global and broken down according to the relationship and the severity)
- ◆ Number and percentage of subjects with at least one Serious Adverse Event, with the frequencies of each type of event (global and broken down according to the relationship and the severity of the event).
- ◆ Description between groups.

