A study using influenza HA vaccine (BIKEN HA, FLUBIK HA, FLUBIK HA Syringe) was conducted in Japan to evaluate the safety and immunogenicity when two doses of BK-FLU (Influenza HA vaccine (quadrivalent)) were subcutaneously administered into Japanese adults. A total of 55 subjects involved in this study. When two doses of BK-FLU were subcutaneously administered, side reactions were reported in 47 cases out of 55 cases (85.5%). Local reactions at the injection site and systemic side reactions were reported in 47 cases (85.5%) and 8 cases (14.5%) respectively. Nevertheless, no serious adverse events were reported. When the positive conversion ratio of HI antibody titer and neutralization antibody titer, the GMP change rate, and the antibody prevalence rate were calculated, the production of antibody to all the four strains was observed, including subtype A (H1N1) strain, subtype A (H3N2) strain, subtype B (Yamagata lineage) strain, and subtype B (Victoria lineage). It is considered that BK-FLU is safe when 0.5 mL of this investigation product is subcutaneously administered into Japanese healthy adults at the age of not less than 20 years and less than 65 years old twice at an interval of 1 to 4 weeks. Besides, it is confirmed that BK-FLU produces the antibody to all the four strains was observed, including subtype A (H1N1) strain, subtype A (H3N2) strain, subtype B (Yamagata lineage) strain, and subtype B (Victoria lineage). Based on this study, quadrivalent influenza HA vaccine which produced by BIKEN has been registered in Japan.

---

 The Research Foundation for Microbial Diseases of Osaka University. Clinical Trial for BK-FLU on Healthy Adults. (not published)

---

---

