## **6.3. Safety Data Collection and Management Procedures**

The safety data will be collected up to one month after the one injection. During this period, each patient will be provided with a diary card to record the appearance, the duration and the intensity (coded 1,2 or 3) of any local reaction and any systemic event expected or not. The intensity of local reactions will be assessed using a plastic bangle presented in Appendix 4.

For any subject, a local reaction is defined as the occurrence of one or several reaction(s) (expected or unexpected) at the injection site within 28 days following vaccination. Local reactions are:

- ↳ **Local pain**
- ↳ **Redness**
- ↳ **Induration**
- ↳ **Swelling**
- ↳ **Other local reactions**

For any subject, a systemic event is defined as the occurrence of one or several symptom(s) (solicited and unsolicited) within 28 days following vaccination. Systemic events are:

- ↳ **Fever** (axillary temperature  $\geq 38^{\circ}\text{C}$ )
- ↳ **Fatigue**
- ↳ **Muscle pain (Myalgia)**
- ↳ **Other systemic events**

Parents/subjects will measure the intensity of local reactions in using a plastic bangle (See appendix 4). The intensity will be coded in the Diary and CRF as follows:

---

---

|                                                                 | 1=Mild                                      | 2=Moderate                                                  | 3=Severe                                        |
|-----------------------------------------------------------------|----------------------------------------------------|--------------------------------------------------------------------|--------------------------------------------------------|
| Local pain for infants and children (6-35 months)        | Reacts when site is touched                        | Cries when site is touched                                         | Cries when limb is moved                               |
| Local pain for subjects <math>\geq 3</math> years of age | Mild pain to touch                                 | Pain with movements                                                | Significant pain at rest                               |

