#### **7.2.2. Parameters to be measured**

a. GMT, seroprotection and seroconversion rates before and after one dose of immunization will be described per antigen per group vaccine with 95% confidence interval (CI).

b.1 Local reactions and systemic events occurring within 30 minutes after vaccination, 72 hours after vaccination and unexpected event rates, which occurred after 72 hours will be assessed per antigen and per group vaccine with 95% CI.

Any Serious Adverse Events occurring over the study period will be described.

**Subjects** will record the presence of any local or systemic symptom within 28 days following each injection in the diary card. They will answer all questions in the diary for expected and unexpected events during this period.

**The investigator** will report the following data in the CRF:

- The start and end dates of all events.
- The severity (code 1, 2 or 3) of all local reactions.
- Site of local reactions.
- The severity (code 1, 2 or 3) of all systemic events.
- The exact daily maximal axillary temperature up to 3 days after the vaccination.
- The exact maximal axillary temperature of any other fever period.
- The action taken.

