### Appendix 3: Plastic bangle model

Group II (13-17 years old ) and

Group III (18-40 years old)

This bangle will be printed on a transparent plastic square and will be used to assess the intensity of local reactions, which may occur after the injection of vaccine. The bangle is composed of one 10 cm diameter circle and one 5 cm diameter circle. These two circles are concentric and the cross corresponds to the center of the circles.

This plastic bangle will be given to the health worker with instruction for use, as follows :

1. Place the cross at the center of the reaction (middle of the largest diameter, see diagram)
2. Do not press on the plastic square so as not to increase the diameter of the reaction.
3. Note the intensity (1, 2 or 3).

Intensity 1 and 2 are represented by the circle that completely encircles the largest diameter of the reaction. If the largest diameter of the reaction goes outside the biggest circle, the intensity is 3.

For example, in this figure, the intensity is coded 2.

[figure not shown]

---

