### **Plastic Bangle (for infants and children)**

Group I (9-12 years)  
Group IV (6-35 months)  
Group V (3-8 years)

This bangle will be printed on a transparent plastic square and will be used to assess the intensity of local reactions, which may occur after the injection of vaccine. The bangle is composed of one 5 cm diameter circle and one 2.5 cm diameter circle. These two circles are concentric and the cross corresponds to the center of the circles.

This plastic bangle will be given to the health worker with instruction for use, as follows:

1. Place the cross at the center of the reaction (middle of the largest diameter, see diagram)
2. Do not press on the plastic square so as not to increase the diameter of the reaction.
3. Note the intensity (1, 2 or 3).

Intensity 1 and 2 are represented by the circle that completely encircles the largest diameter of the reaction. If the largest diameter of the reaction goes outside the biggest circle, the intensity is 3.

[figure not shown]

For example, in this figure, the intensity is coded 2.

---

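### The safety analysis breaks local reactions down by size alone, so the recorded grade of local pain is used in no specified table

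*Protocol*

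**What the plan says.** Section 6.3 gives local pain its own three-step scale in two age versions. The top step is "Cries when limb is moved" at 6 to 35 months and "Significant pain at rest" from 3 years. Neither involves a measurement in centimetres. Redness, swelling, induration and other local reactions are coded 1 to 3 by where the reaction falls relative to two concentric circles on a plastic bangle.

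Section 7.2.2 requires the investigator to enter in the CRF: "The severity (code 1, 2 or 3) of all local reactions". The pain grade is therefore collected.

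The Safety analysis list in section 8.1.3.2 then sets the tabulation for each class of event. Both local-reaction bullets (up to 72 hours, and 72 hours to one month) give frequencies by type, "global and broken down according to the size of the reaction when appropriate". Both systemic-event bullets read "global and broken down according to the relationship and the severity", and the serious adverse event bullet has the same two criteria.

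Appendix 3 defines two bangles. For Groups II and III (13 to 40 years): "The bangle is composed of one 10 cm diameter circle and one 5 cm diameter circle". For Groups I, IV and V, which include the 9 to 12 year olds of Sub-study A: "The bangle is composed of one 5 cm diameter circle and one 2.5 cm diameter circle".

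**The concern.** The protocol names a breakdown for every class of event, and for local reactions it names one that cannot be applied to pain. The qualifier on appropriateness restricts the size breakdown to reactions that have a size. It puts nothing in its place for pain. A table built to this rule shows how many subjects had pain and stops there.

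Comparing the safety of QIV with TIV, and of three QIV batches, in subjects aged 9 to 40 years is a secondary objective (section 2.2). If one vaccine or batch caused more severe pain at a similar overall frequency of pain, the specified output would not reveal it, although the data would be in the database.

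A lesser matter concerns reactions that do have a size. Sub-study A uses two bangles, so a table that presents the codes as size over 9 to 40 years would combine different diameters under one code.

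**Working it through.** The protocol states no figure to reproduce on this point. The check sets the passages side by side, with a little arithmetic.

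**Step 1. What is collected and what is tabulated**

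| Event class | Grade recorded | Breakdown specified in 8.1.3.2 |
|---|---|---|
| Local pain | 1 to 3 (6.3, 7.2.2) | none applicable (size only) |
| Redness, swelling, induration, other local | 1 to 3, from the bangle | size, where appropriate |
| Systemic events | 1 to 3 | relationship and severity |
| Serious adverse events | – | relationship and severity |

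Sections 7.2.1 and 7.2.2 were checked for a rule that fills the empty cell. For reactions they list only occurrence rates by time window, per vaccine group. No listed analysis uses the pain grade.

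**Step 2. What the specified pain row can show**

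The row is a count over the arm size. For illustration only, assume that 20.0% of an arm reports pain. This borrows the rate of any local reaction in the 2008 trivalent study (section 1.5), because no pain rate is given. Then 0.200 × 135 = 27 subjects. The row reads 27 of 135 whether all 27 are grade 1 or all 27 are grade 3. At that frequency, grade 3 pain could lie anywhere from 0 to 27 subjects (0% to 20.0%) without changing the output.

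**Step 3. Reach**

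Pain is graded at every age, so the gap covers 540 + 270 = 810 planned subjects and both time windows. In Sub-study A all subjects are aged 3 years or more and share one pain scale. Pain grades pooled over 9 to 40 years would therefore have a single meaning. In Sub-study B the two pain scales coincide with Groups IV and V.

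**Step 4. The bangle codes in Sub-study A**

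The circles are 2.5 and 5 cm in Group I, and 5 and 10 cm in Groups II and III.

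| Largest diameter | Code, Group I | Code, Groups II and III |
|---|---|---|
| up to 2.5 cm | 1 | 1 |
| over 2.5 to 5 cm | 2 | 1 |
| over 5 to 10 cm | 3 | 2 |
| over 10 cm | 3 | 3 |

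If pooled and read as size, code 2 spans 2.5 to 10 cm, and code 3 means over 5 cm in one group and over 10 cm in the other two. The planned mix is 45/135 = 33.3% on the small bangle and 90/135 = 66.7% on the large one. It is the same in all four arms, because section 3.1 plans 45 subjects per arm in each age group.

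**The case against.** The strongest reply is that section 8.1.3.2 does not say size is the only breakdown allowed. Pain is graded and recorded, the list ends with an open promise to describe differences between groups, and the layout of descriptive safety tables is commonly left to the SAP, which is not shown here. A table of pain by grade would contradict nothing. This stands as far as it goes: the protocol does not order the grade to be discarded, and the SAP may already include it. But the protocol did not leave the breakdown open. It chose one for each event class, named severity for two of them, and named for the third a criterion that pain cannot meet.

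Three stronger readings are tempting, and the documents do not support them.

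- *That the two bangles bias QIV against TIV or batch against batch.* The planned bangle mix is identical in every arm, so it does not. Only the meaning of a pooled size and comparisons between ages are affected.
- *That the bangles are an error, or that pooling of size codes is planned.* Appendix 3 sets out two age-specific scales openly. A code that changes meaning with age follows from any age-banded severity scale. Pooling over 9 to 40 years is suggested by the objective but stated nowhere. Section 7.2.2 does not list a diameter among the items reported, but the CRF is not shown, so it cannot be said that none is recorded.
- *That the number affected can be read from earlier studies.* Section 1.5 says of the Japanese quadrivalent product: "Local reactions at the injection site and systemic side reactions were reported in 47 cases (85.5%) and 8 cases (14.5%) respectively". That study had 55 adults given two subcutaneous doses, whereas Sub-study A gives one intramuscular dose. The figure also counts any local reaction, not pain. It supports interest in local reactions, not an expected count here.

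**Conclusion.** The point holds as a defect in a stated analysis rule. The pain grade is collected, but no specified table uses it, so the output as written cannot show a difference in severe pain between vaccines or batches. The gap extends to both local-reaction bullets and all 810 planned subjects. The number of pain cases involved is unknown.

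This rests on taking the list in section 8.1.3.2 as the planned output. If the SAP already tabulates pain by grade, only the protocol wording needs aligning. No data are lost and no primary result is touched, so this is an improvement at almost no cost rather than a flaw that endangers the trial.

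The bangle matter is minor, and arises only if the codes are presented as size across Groups I to III.

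**What to change.** In both local-reaction bullets of section 8.1.3.2, replace the size criterion with the intensity code (1, 2, 3). State that the number and percentage of subjects at each grade, including grade 3 pain, will be given per vaccine arm and per injection.

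If codes for redness, swelling or induration are shown for 9 to 40 years together, either present them by bangle age group (Group I; Groups II and III) or label them as age-specific severity grades rather than sizes.

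The cost is one wording change in two bullets and a few table rows. The codes are already due to be recorded in the diary and CRF. No grading scale, visit or procedure changes.

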## **8.2. Data Management**

Throughout regular data collection and monitoring, clinical data reported on CRFs and/or relevant serological/biological samples analysis results scheduled in the protocol will be integrated into a clinical data management system.

For each batch of data, single entry, quality control and triggers to computerized logic and/or consistency checks will be systematically applied in order to detect errors or omissions. After integration of all corrections in the complete set of data, the data based will be locked and saved before being released for statistical analysis.

Each step of this process will be monitored through the implementation of individual passwords and/or regular backups in order to maintain appropriate database access and to guarantee database integrity.

---

---

## **9. Confidentiality, Stipends and Adverse Events Compensation and Insurance**

### **9.1. Confidentiality**

#### **9.1.1. Confidentiality of Data**

Prior to initiation of the trial, the investigator will sign a fully executed confidentiality agreement with Bio Farma.

#### **9.1.2. Confidentiality of Patient Records**

Confidentiality of patient records will be ensured by identifying documents using inclusion number and subject initials (first three letters of the subject's name).

### **9.2. Stipends for Participation**

Not applicable.

### **9.3. Adverse Events Compensation and Insurance**

Bio Farma shall insure all clinical trial subjects and investigators and cover medicinal treatment expenses and/or compensation to clinical trial subject to anticipate any serious adverse events or adverse events as consequence of their participation on this clinical study. Bio Farma shall not be liable for all claims from third parties caused by or resulting from malpractice and/or negligence or willful misconduct of investigators and its staff.

If there is any doubt raised by cause and effect relation between adverse reactions and their participation on this clinical study, judgment of Indonesian Vaccine Safety Advisory Committee or NRA shall be needed.

---

---

## **10. Publication Policy**

The final report will be prepared by a publication committee which includes the investigators and representatives of Bio Farma. It will be signed by the coordinating (or principal) investigator. Publication will not reasonably withhold.

---

## 12. Appendices

The following is a non-comprehensive list of possible appendices

**Appendix 1:** Personnel involved in the Trial

**Appendix 2:** SAE reporting form

**Appendix 3:** Plastic bangle

---

## Appendix 2: Sample SAE reporting forms

### FORMULIR PELAPORAN KEJADIAN IKUTAN PASCA IMUNISASI (KIPI)

Kode sumber data : .....

Tgl.terima : .....

#### PASIEN

Nama : ..... Tanggal lahir: ...../...../..... Penanggung jawab (dokter)  
 Nama Orangtua : ..... Jenis kelamin: .....  
 Alamat : ..... Laki-laki ..... ☐ Alamat (RS, Puskesmas, Klinik)  
 ..... Perempuan ..... ☐ .....  
 ..... Bagi Wanita Usia Subur (WUS): .....

Kota : ..... Hamil ..... ☐ Prop. : .....  
 RT/RW : .....Kel..... Tidak hamil ..... ☐ Telp. : .....  
 Prop. : ..... Tidak tahu ..... ☐ .....  
 Kota : .....Kode Pos.....  
 Telp. : .....

Pemberi imunisasi: Dokter/bidan/perawat/jurim

#### Daftar vaksin yang pernah diberikan dalam 4 minggu terakhir, termasuk imunisasi terakhir

| Jenis vaksin | Pabrik | No.Lot/Batch | Pemberian                   |              |                   | Tempat pemberian imunisasi (*) |
|--------------|--------|--------------|-----------------------------|--------------|-------------------|--------------------------------|
|              |        |              | Cara tetes oral/i.m/s.c/i.c | Jumlah dosis | Tanggal imunisasi |                                |
| 1            |        |              |                             |              |                   |                                |
| 2            |        |              |                             |              |                   |                                |
| 3            |        |              |                             |              |                   |                                |
| 4            |        |              |                             |              |                   |                                |

(\*) Tempat pemberian imunisasi di:

1. Dokter Praktek/RS 2. Puskesmas 3. Posyandu 4. Balai Pengobatan/Bidan 5. Balai Imunisasi 6. Sekolah 7. Dll

(sebutkan)

#### Manifestasi kejadian ikutan (keluhan, gejala klinis)

|                                                                | Waktu Mulai | Lamanya |     |    | Keterangan lanjutan hasil akhir:                                                                                                                                                              |
|----------------------------------------------------------------|-------------|---------|-----|----|-----------------------------------------------------------------------------------------------------------------------------------------------------------------------------------------------|
|                                                                |             | Mm      | Jam | Hr |                                                                                                                                                                                               |
|  Kesadaran menurun                     |             |         |     |    | Pasien meninggal tgl.: ...../...../.....
Sakit
Perlu tindakan darurat/dokter
Perlu perawatan RS (.....hari)
Sembuh
Belum sembuh
Tidak diketahui
Lain-lain .....
..... |
|  Kejang-kejang                         |             |         |     |    |                                                                                                                                                                                               |
|  Demam tinggi lebih sehari             |             |         |     |    |                                                                                                                                                                                               |
|  Adanya kelumpuhan atau kelemahan otot |             |         |     |    |                                                                                                                                                                                               |
|  Infeksi berat ditempat injeksi        |             |         |     |    |                                                                                                                                                                                               |
|  Infeksi berat diluar tempat injeksi   |             |         |     |    |                                                                                                                                                                                               |
|  Reaksi alergi:                        |             |         |     |    |                                                                                                                                                                                               |
|  - pembengkakan bibir & tenggorokan    |             |         |     |    |                                                                                                                                                                                               |
|  - sesak nafas                         |             |         |     |    |                                                                                                                                                                                               |
|  - erythema                            |             |         |     |    |                                                                                                                                                                                               |
|  - papula                              |             |         |     |    |                                                                                                                                                                                               |
|  - tekanan darah menurun               |             |         |     |    |                                                                                                                                                                                               |
|  Diare                                 |             |         |     |    |                                                                                                                                                                                               |
|  Muntah                                |             |         |     |    |                                                                                                                                                                                               |
|  Encephalopathy (*)                    |             |         |     |    |                                                                                                                                                                                               |
|  Meningitis dan atau encephalitis (*)  |             |         |     |    | (*) Ditentukan berdasarkan
diagnosa dokter                                                                                                                                                 |
|  Kelumpuhan (*)                        |             |         |     |    |                                                                                                                                                                                               |
|  Trombositopenia (*)                   |             |         |     |    |                                                                                                                                                                                               |
|  Lain-lain: .....                      |             |         |     |    |                                                                                                                                                                                               |

Pengobatan yang diberikan:

☐ ..... ☐ ..... ☐ .....

Riwayat efek samping obat/vaksin yang pernah dialami:

Obat-obatan yang diberikan bersamaan:

☐ ..... ☐ ..... ☐ .....

Data laboratorium (bila ada)

Penyakit yang diduga diderita pada saat vaksinasi (spesifik)

Diagnosa dokter tentang:

Alergi, kelainan sejak lahir, pengobatan khusus (spesifik):

ada/tidak

Bila ada sebutkan: .....

|                                                                        |                                                                   |
|------------------------------------------------------------------------|-------------------------------------------------------------------|
| Waktu penerimaan laporan Kejadian Ikutan
Tanggal: ...../...../..... | ....., tgl. ....../...../.....
Tanda Tangan Pelapor

( ) |
|------------------------------------------------------------------------|-------------------------------------------------------------------|

